### Study design

The study uses an Interrupted Time Series (ITS) Design [21, 22] with a duration of 15 months. All trials start in the control phase of randomized length with regular recruitment and change to the intervention phase with additional IT support, ensuring a minimum of one month in each phase and a minimum trial observation of 6 months. At least one month prior to the inclusion of *a* specific trial into the study, the length of the control phase for this trial is randomized centrally across all 10 sites. A block randomization was used to randomize the time of switching to the new scheme in the percentage of the planned enrollment time into the study. We used R version 4.1.2 and the package blockrand version 1.5 with the seed 9384902. We allowed for values between 0.15 and 0.85 with 0.05 steps, rounding the resulting time of switching to the first or 15th of a month. We generated 5 blocks with a size of 30 resulting in 150 ids. When a study was enrolled at one of the sites, the site contacted the independent person at Freiburg, who took the next free id from the randomization list and relayed the time of switching for the specific study. The persons responsible for enrollment had no access to the randomization list.

Due to the embedding of the intervention into and its overlap with the recruitment processes, it is practically not feasible to completely blind the study. Nevertheless, the randomized time point to switch to the intervention will only be disclosed to the sites 2 months before and only subsequently to the medical staff. The effectiveness will be measured by the number of recruited participants per trial and week standardized by the targeted number of participants to be recruited into the specific trial. This will be analyzed by means of a linear mixed model. In addition, user interviews will be conducted prior to the start of the intervention and at the end of the study. 

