#### Sample size calculation

Sample size calculation is based on the assumption of a simple parallel group design. On a significance level of 5% and a power of 80%, an effect size of *d*=0.57 can be demonstrated with a two-sided *t*-test in a balanced design with a total number of 100 trials (10 per site). Even if this effect can be classified as strong, the dynamic Interrupted Time Series design offers more statistical power than a two-group t-test, especially when the number of data points is relatively large and the effect size is not small, as is expected in our case. This added power in the ITS design is mainly due to its methodology as it incorporates the temporal ordering of observations, which allows it to account for time-related effects. Thus, it can potentially provide a more accurate estimate of the intervention effect, especially when considering various variability factors (time, location). In addition, we aim to include as many trials as possible, potentially exceeding the total number of 100.

To assess the feasibility of this number, we searched ClinicalTrials.gov for trials registered and actively recruiting that began recruitment on 01-01-2021 or earlier and whose primary completion date is 01-01-2023 or later. Table 1 shows the results per site.

**Table 1 Tab1:** Number of recruiting trials at the participating sites with a start date on or before 01-01-2021 and primary completion on or after 01-01-2023 with the location filter set to the city name of the site

Site	Number of trials on ClinicalTrials.gov satisfying criteria for feasibility estimation
University Hospital Dresden	185
University Hospital Erlangen	214
University Hospital Frankfurt	189
University Hospital Freiburg	103
University Hospital Gießen	73
University Hospital Greifswald	29
University Hospital Magdeburg	58
University Hospital Mainz	116
University Hospital Mannheim	75
University Hospital Marburg	66

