### Generation and implementation of allocation

Prior to the inclusion of *a specific* trial into the study, the length of the control phase for this trial is randomized centrally across all 10 sites. The overall observation period of the trials varies between 6 and 15 months. With a pseudo-random generator from the R-statistical package, the length of the control phase is randomly assigned to a value between 15% and 85% of the total observation period, which ensures that for short (6 months) trials control or intervention phases have at least a duration of one month. Respectively, a trial with an observation time of 15 months has control or intervention phases with a minimum length of 2.5 months. For each trial, an exact date for the start of the intervention phase is calculated from the inclusion date of the trial and the duration of the control phase.

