### Data collection

The following data is collected for each trial:

Trial specific parametersParticipating sitesRegistration information: unique trial identifier such as the ClinicalTrials.gov NCT number, the DRKS number, or the Universal Trial Number (UTN)Start of recruitmentPlanned and actual end of recruitmentExpected duration of recruitmentTargeted participant countExpected number of participants at each siteNumber of participants already recruited at the beginning of the studyTrial typeInclusion criteriaExclusion criteriaPersons (or groups) involved in recruitmentNumber of patients who were admitted to the site on a monthly basis as in- or outpatients

During the intervention:Number of screenings conductedNumber of recruited participants per weekNumber of recruitment proposals per week (automatically recorded by the IT-solution)Number of recruited participants not suggested by the system per week (i.e., only through standard recruitment procedures)

After the intervention:

Short interviews and surveys on the usability of the system are conducted with one user for each trial. To quantify the user experience and usability of the tool, the System Usability Scale (SUS) [25] and the User Experience Questionnaire - short (UEQ-S) [26] will be used.

Per recruitment proposal:

The following data is collected for each recruitment proposal. A suitable feedback mechanism for reporting trial inclusions must be established individually at the centers.Organizational unit of the site where the inclusion took place (automatically recorded by the IT system)Status as indicated in the recruitment list.“Recruitment Proposal”“Under consideration”“Does not meet eligibility criteria”“Is Participating in trial”“Not willing to participate”Outpatient or inpatient status at the time of inclusion

The patient inclusion data is primarily collected via the trial’s existing electronic documentation and transferred to custom data entry masks. To ensure the completeness of data collection, the documentarians from MIRACUM are in close exchange with the corresponding staff in the departments and trial personnel.

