### Statistical methods

The characteristics of the included studies will be presented in tabular form. All variables will be summarized using appropriate summary statistics. The mean, standard deviation, and the quantiles will be used for continuous variables and absolute and relative frequencies for categorical variables. If applicable, the variables will be visualized using boxplots and histograms, potentially over time.

The primary analysis will be conducted using linear mixed models with the actual recruitment number per week and trial standardized by the expected recruitment number per week and trial as the dependent variable. The choice is driven by the model’s ability to account both for fixed effects and random effects. This flexibility of this model is particularly suited for capturing the hierarchical structure in our data and aligns with the nature of the ITS design, where repeated measures over time and within-trial correlations are essential. A positive and statistically significant fixed effect of the binary variable “intervention allocation per week” will be interpreted as the measure for effectiveness. The corresponding effect will be evaluated for significance on the 5% level using the likelihood-ratio test. The model will be adjusted for trial, site, season, and time via random effects. Primarily, compound symmetry is considered as a working covariance matrix (constant correlation between time points), while autoregressive and unstructured covariance matrices are used as sensitive analysis. Additional sensitive analysis involves larger time frames, i.e., per month instead of per week, other distributions and link functions, i.e., generalized models, and classical statistics via mean values. Given the conservative sample size calculation based on a *t*-test, the linear mixed model is backed with adequate statistical power given the expected heterogeneous nature of the data.

To uncover further correlations and generate hypotheses, explorative analysis is carried out, including specific evaluation of site and trial characteristics.

No deviations from the protocol or missing data are expected. Trials are otherwise excluded from the primary analysis and their characteristics are compared to the other trials to identify potential problems for generalizability of the results.

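### The primary model makes no use of each trial's pre-study recruitment rate, although the needed items are largely collected; adding it is an optional gain of about 1–7% in the variance of the intervention effect

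*Protocol article*

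**What the plan says.** The primary analysis (protocol article, Statistical methods) is a linear mixed model for the weekly recruitment count divided by the trial's expected weekly count. The effect is the fixed coefficient of the weekly intervention indicator. On adjustment the section says: "The model will be adjusted for trial, site, season, and time via random effects". The working covariance is compound symmetry. Trial characteristics appear only in the exploratory analysis.

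The design is within-trial: "All trials start in the control phase of randomized length with regular recruitment and change to the intervention phase with additional IT support" (Study design). In Generation and implementation of allocation, "the length of the control phase is randomly assigned to a value between 15% and 85% of the total observation period", and "The overall observation period of the trials varies between 6 and 15 months".

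Data collection lists, for each trial, the start of recruitment, the targeted count, the expected duration, the expected number at each site, and the number of "participants already recruited at the beginning of the" study. The feasibility search under Sample size calculation looked for "trials registered and actively recruiting that began recruitment on 01-01-2021 or earlier". That describes a registry search and not the trials enrolled, but it shows that trials with a recruitment history were in view.

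**The concern.** A trial that recruited well or badly against its target before the study will tend to go on doing so. For trials with a history, the listed items give that earlier level on the scale of the primary outcome. The planned model must instead learn each trial's level from the observation weeks alone.

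A random trial intercept is not a fixed trial effect. The mixed model combines two sources of information on the intervention: the change within each trial, and the comparison of trials that spent different shares of their time under intervention. The second source is blurred by unexplained differences in trial level. A covariate that explains part of those differences sharpens it. At stake is a little precision, and nothing else.

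**Working it through.** **The plan's own figure.** The sample size section says that d = 0.57 "can be demonstrated with a two-sided *t*-test in a balanced design with a total number of 100 trials (10 per site"). With 50 trials per group and two-sided 5%, d = 0.57 gives power 0.806 (t distribution), and the effect detectable with 80% power is 0.566. The figure reproduces. It belongs to a parallel-group t-test, so it does not give the power of the mixed model.

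**How much between-trial information there is.** Take trials of equal length n, residual variance s², trial variance τ², intervention share q and, for now, no time effects. The information on the effect per trial is

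(n/s²) × { E[q(1−q)] + (1−w) Var(q) }, with w = nτ²/(s² + nτ²).

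The first term is within-trial and the second between-trial. A baseline covariate acts only on w, by replacing τ² with τ²(1−R²), where R² is the share of trial-level variance that it explains.

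- From the protocol: q takes 15 values from 0.15 to 0.85 in steps of 0.05. So Var(q) = 0.05² × (15² − 1)/12 = 0.0467 and E[q(1−q)] = 0.25 − 0.0467 = 0.2033.
- Assumed: n = 45 weeks (the middle of 26–65), e = 0.5 expected recruits per week with s² = 1/e = 2, and τ² = 0.10.
- Without the covariate: w = 4.5/6.5 = 0.692, and the bracket is 0.2033 + 0.308 × 0.0467 = 0.2177.
- With R² = 0.5: w = 2.25/4.25 = 0.529, and the bracket is 0.2033 + 0.471 × 0.0467 = 0.2253.
- Variance ratio: 0.2177/0.2253 = 0.966, a fall of 3.4%.
- A perfect covariate (w = 0) would give 0.2177/0.25 = 0.871, so in this setting the ceiling is about 13%.

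**With time effects.** Adding week, season and site effects shifts some weight to the between-trial comparison. Generalised least squares over 100 trials at 10 sites, 26–65 weeks each, with R² = 0.5 gives:

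| ICC of the weekly outcome | SE ratio | Fall in variance (1 − ratio²) |
|---|---|---|
| 0.05 | 0.964 | 7.1% |
| 0.1 | 0.970 | 5.9% |
| 0.3 | 0.987 | 2.6% |
| 0.5 | 0.994 | 1.2% |
| 0.7 | 0.997 | 0.6% |

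Beyond an ICC of about 0.1 the gain shrinks as trials differ more, because the trial effect then does more of the work. In a parallel-group comparison the SE ratio at R² = 0.5 would be √0.5 = 0.71.

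**What R² is plausible.** Sampling error in the prior count limits it. The reliability is τ²/(τ² + 1/(eW)) for W pre-study weeks. If the trial level correlates only 0.8 over time, multiply by 0.8² = 0.64.

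- e = 0.5, τ² = 0.10, W = 21: 0.10/(0.10 + 0.095) = 0.51; with drift 0.33.
- The same with W = 52: 0.10/(0.10 + 0.038) = 0.72; with drift 0.46.
- Extremes: e = 0.25, τ² = 0.10, W = 21 gives 0.34 (with drift 0.22); e = 1, τ² = 0.25, W = 52 gives 0.93 (with drift 0.59).

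With drift, R² is therefore 0.22–0.59. Over that range, with calendar month as a random effect, the variance of the intervention effect falls by 1.3–7.4%. A Poisson simulation that set trials without history to the mean plus an indicator gave falls of about 2–3% with correlation 0.8, and 5–9% with perfectly stable levels. It showed no visible bias.

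**In terms of power.** If a comparison has 80% power, effect/SE = 1.960 + 0.842 = 2.802.

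- A fall of 1.3% gives 2.802/√0.987 − 1.960 = 0.860, or power 80.5%.
- A fall of 7.4% gives 2.802/√0.926 − 1.960 = 0.951, or power 82.9%.
- As a number of trials: 1/0.987 = 1.013 and 1/0.926 = 1.080, or about 1 to 8 more per 100.

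**The case against.** The strongest reply is that the problem is largely solved already. The intervention varies within trial, the model adjusts for trial, and the outcome is scaled by the trial's own expected rate. When one phase is as short as 15% of 6 months (about 4 weeks), the other is about 22 weeks, and the trial's level is learned from both. This stands, and it is why the gain is a few percent and not what a parallel-group design would show. It does not bring the gain to zero.

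A further reply is that a precision covariate is a detail that an article may leave to the analysis plan. That is fair, and nothing in Statistical methods is wrong or contradictory on this point.

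A reader might infer more than the documents support:

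- **That between-trial noise stays in the effect estimate.** Most of it is removed by the within-trial design.
- **That power would rise from 80% to about 88%.** That needs R² = 0.8 together with time effects that act like fixed calendar-month terms. The plan has time as a random effect, and R² = 0.8 is out of reach in the setting worked above, where reliability is at most 0.72. The protocol's 80% is also that of the t-test.
- **That the adjustment cannot bias the contrast.** Under Study design the switch is randomized at least one month before inclusion and disclosed to sites 2 months ahead. A 6-month trial with a 15% control phase switches 0.9 month after inclusion, so disclosure can come about 1.1 months before inclusion. A count taken at inclusion is then not strictly a baseline value. Any effect is probably small, but there is no guarantee.
- **That it costs one degree of freedom and no new data.** It takes two parameters. The prior count is also listed without saying whether it is for the site or the whole trial. Its date is the beginning of the study, although under Recruitment trials enter dynamically.

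**Conclusion.** The point holds as an optional efficiency gain. The primary model leaves out a baseline value of its own outcome that can be formed, for trials with a history, from items the study already lists. Using it would lower the variance of the intervention effect by about 1–7%, and by up to about 9% if recruitment levels are very stable. Where power would otherwise be 80%, it would become about 80.5–83%.

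These figures rest on assumed values for the between-trial variance, the expected weekly counts, the length of the prior history, the stability of recruitment and the size of the time effects. The documents give none of these. The share of trials entering without any history is also unknown, and a large share would reduce the gain. The planned analysis is valid without the change.

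**What to change.** In Statistical methods, add one fixed covariate to the primary linear mixed model, the pre-study recruitment ratio:

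(participants already recruited at the site / weeks of prior recruitment at the site) / expected recruits per week.

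For trials with no prior recruitment, set it to the mean of the others and add a 0/1 indicator, so that no trial is lost.

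In Data collection, define the prior count and the start of recruitment for the site concerned. Count prior recruits up to a date no later than that trial's randomization, or at least before its switch date is disclosed, so that the covariate is a true baseline value.

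The cost is two extra parameters, a sentence in the analysis section and a data item clarified as to site and date. No further trials are needed.

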### Outcomes

#### Primary outcome

Absolute and relative difference in the recruitment numbers of the observed studies before and after the intervention, in relation to the actual recruitment time. The primary outcome is the number of participants recruited per trial and week standardized by the targeted number of participants per week and the expected recruitment duration of the specific trial (actual recruitment number in week *i*/expected recruitment number per week, where expected recruitment number per week = target number of cases/duration of the trial in weeks and *i*=1, ..., observation period in week *i*, *j*=trial 1, ...,5, *k*=site 1, ...,10).

To account for site-specific and seasonal effects, a mixed model will be used.

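### Time and season enter the primary model only as random effects, so with a one-way switch part of any common drift in recruitment biases the tested intervention coefficient

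*Protocol article*

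**What the plan says.** Under Study design, the protocol article has a single switch in one direction: "All trials start in the control phase of randomized length with regular recruitment and change to the intervention phase with additional IT support". The switch point is randomized as a fraction of the planned observation: "We allowed for values between 0.15 and 0.85 with 0.05 steps". Under Generation and implementation of allocation, observation lasts 6 to 15 months. Under Recruitment, trials may join at different dates.

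Under Statistical methods, the dependent variable is the weekly recruitment count divided by the expected weekly count. The weekly binary intervention indicator is the only fixed effect named. A positive coefficient that is significant at 5% in a likelihood-ratio test counts as effectiveness. Then: "The model will be adjusted for trial, site, season, and time via random effects". Under Primary outcome the purpose is given as: "To account for site-specific and seasonal effects, a mixed model will be used". The listed sensitivity analyses change the covariance matrix, the time unit, the distribution or link, or use mean values. None is said to add a fixed time term.

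Under Sample size calculation, the design is defended on the ground that "it incorporates the temporal ordering of observations, which allows it to account for time-related effects".

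**The concern.** Because no trial returns to control, the intervention indicator rises with time inside every trial. A random time effect is centred on zero, shrunk towards zero and treated as independent of the indicator. When recruitment drifts across all trials, it takes up only part of the drift and the tested coefficient takes the rest.

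The season effect offers little protection. If observation runs 15 months from 1 June 2021, only summer occurs twice, so season is largely another label for calendar time. A different covariance matrix or link does not put a time trend into the mean model.

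The only confirmatory conclusion rests on this coefficient. An upward drift could make an ineffective tool look effective; a downward drift could hide a useful one.

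**Working it through.** **1. The plan's own figure.** The article states that "an effect size of *d*=0.57 can be demonstrated" "in a balanced design with a total number of 100 trials (10 per site". With 50 trials per group, power ≈ Φ(d·√(n/2) − 1.96) = Φ(0.57 × 5 − 1.96) = Φ(0.89) = 81.3%. The exact t-test gives 80.6%, and the detectable d at 80% power is 0.566. The figure reproduces and does not depend on this point.

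**2. How far intervention and time coincide.** For a trial observed for length L and switched at fraction f, mean intervention time is (1 + f)L/2 and mean control time is fL/2. The difference is L/2 for every f. The pooled within-trial correlation of indicator and time is √(3 × mean[f(1 − f)]). For f = 0.15 to 0.85 in steps of 0.05, mean f(1 − f) = 0.25 − 0.0467 = 0.2033, so the correlation is √0.61 = 0.78. It is high but below 1, so the two can be separated.

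**3. Bias with no time adjustment.** Assume a mean ratio of 0.7 and a 20% rise over 15 months, that is 0.14. If all trials run 15 months, the false effect is 0.5 × 0.14 = 0.07.

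**4. Simulation A: the model as written, no tool effect.** From the article: 100 trials, 10 sites and the 15 switch fractions. Assumed: Poisson weekly counts, mean ratio 0.7, between-trial variance about 0.2, 0.5 expected recruits per week. Fits were by maximum likelihood with likelihood-ratio tests, 200 runs per setting. Where two values appear, the second is a repeat under the same assumptions.

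| Setting | Mean estimate | Positive and significant (nominal 2.5%) |
|---|---|---|
| No drift | – | 3.0% |
| +20%, staggered 6–15 months | +0.052 (repeat) | 17.5%; 20% |
| +20%, all trials 15 months | +0.067; +0.066 | 52.5%; 57.5% |
| Same, time as a random slope per trial | – | 48.5% |
| +10%, all trials 15 months | – | 15% |
| +20%, all 15 months, 0.25 or 1 expected recruit per week | – | 26.5% or 78% |

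With fixed calendar months the bias was within 0.005 and false positives were 1.5–3.5%. In the repeat, with fixed months or a linear term, they were 0.003–0.011 and 2.5–5%. At 200 runs the Monte Carlo standard error is about 2.7 points at 17.5% and 3.5 points at 50%.

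**5. Simulation B: other readings of random time.** Assumed: mean ratio 0.7, residual SD 0.85, trial SD 0.4, site SD 0.15, drift +0.3 over 15 months (0.3/0.7 = 43%), no tool effect, 100 runs. Cells show the mean estimate and the rejection rate at 5%.

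| Handling of time | Staggered entry | Common start |
|---|---|---|
| No time term | +0.091, 81% | +0.147, 100% |
| Random season and week | +0.085, 74% | +0.133, 99% |
| Random season and month | +0.084, 73% | +0.083, 53% |
| Random season, slope per trial | +0.084, 75% | +0.138, 100% |
| Random season, slope per site | +0.076, 57% | +0.062, 35% |
| Fixed linear calendar time | +0.008, 4% | −0.002, 5% |

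Without drift, all these models rejected in 3–9% of runs.

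**6. Downward drift.** In B with drift −0.3, a true effect of 0.15 and a common start, the estimates were 0.019 (week), 0.068 (month), 0.014 (trial slope) and 0.086 (site slope). They were positive and significant in 7%, 40%, 6% and 55% of runs. Fixed linear time gave 0.150 and 98%. In A with a 20% decline, the bias was −0.064. Power for a true effect of 0.14 is then Φ((0.14 − 0.064)/0.033 − 1.96) = 63%, against Φ(0.14/0.051 − 1.96) = 78% with fixed months.

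**7. Price of the fixed term.** The standard error rises from 0.033 to 0.051 in A (+55%). In B it rises from 0.032 to 0.045 (+41%, staggered) and from 0.025 to 0.037 (+48%, common start). Without drift, power in A for a true effect of 0.14 falls from Φ(0.14/0.033 − 1.96) = 99% to 78%.

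**The case against.** - **The article is condensed, and an unseen SAP may add a fixed trend.** A reader might also assume that a random slope comes with a fixed mean slope. That is possible, but the article states how time enters rather than leaving it open. The primary test should not rest on a guess.
- **No drift is documented.** This stands as a limit on size. The article gives no trend, weekly rate or variance. Its nearest hint is the feasibility search, which counted trials already recruiting; their ageing would point downward, against the tool. That search is not the enrolled sample, since eligibility asks only for a 6-month overlap.
- **Randomized switching already deals with time.** A reader might infer the opposite, that the design cannot separate tool from time. The documents support neither. Staggered random switching lets switched trials be compared with those not yet switched at the same date; the fault lies in the model sentence.
- **Random time effects do absorb some drift.** Correct. A reader might infer that they are shrunk almost to nothing, but this depends on what time means in the model. Random months or site slopes roughly halved the bias under a common start, though they gained little under staggered entry and removed it in neither case.
- **The remedy costs power if there is no drift.** Correct: about 99% to 78% in the example.

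**Conclusion.** The concern holds as a fault in a stated modelling choice. A common drift passes in part into the coefficient that decides the study, in either direction, and the advantage claimed for the design in handling time is not delivered. The mechanism follows from the one-way switch and the random-only time terms. Its size is conditional on assumptions.

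For a 20% rise, a mean ratio of 0.7 and 0.5 expected recruits per week, false claims of effectiveness are about 17–20% under the staggered entry that the protocol describes. A reader might take the 50–58% for all trials running 15 months as the expected rate, but the protocol does not describe that setting. With no drift the model behaves close to nominally. The sample-size figure itself is not in error.

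**What to change.** Under Statistical methods, add calendar time as a fixed effect (month, spline or linear trend) beside the intervention indicator, and keep trial and site as random effects. Carry the same fixed time term into every sensitivity analysis.

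Add a sensitivity analysis with a fixed term for time since inclusion, because entry is staggered and a settling-in pattern follows each trial's own clock. In one check with an assumed settling-in rise of 0.14 (8-week time constant, staggered entry), fixed calendar months still left 0.011 of a 0.049 bias.

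No new data are needed. The standard error rises by about 40–55%, so the statement in the same section that the mixed model has adequate power should be recalculated with the fixed time term included.

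### If weekly recruitment within a trial is positively autocorrelated, the primary likelihood-ratio test under compound symmetry does not hold its 5% level

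*Protocol article*

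**What the plan says.** The Statistical methods section of the protocol article fixes the primary analysis as a linear mixed model. The dependent variable is the weekly recruitment of each trial divided by its expected weekly recruitment. Trial, site, season and time enter as random effects. On the covariance it states "compound symmetry is considered as a working covariance matrix (constant correlation between time points), while autoregressive and unstructured covariance matrices are used" as sensitivity analyses. The binary intervention term is to be "evaluated for significance on the 5% level using the likelihood-ratio test", and a positive, significant coefficient is read as effectiveness. Further sensitivity analyses use monthly instead of weekly frames, generalized models, and classical statistics on mean values.

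Under Generation and implementation of allocation, "The overall observation period of the trials varies between 6 and 15 months", and the control phase is "randomly assigned to a value between 15% and 85% of the total observation period". Each trial therefore crosses once from control to intervention.

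No robust or trial-level variance is named for the primary test. No autocorrelation is given, and no rule says what follows if a sensitivity analysis disagrees.

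**The concern.** Within a trial, the exposure is one long run of control weeks followed by one long run of intervention weeks. Staff changes, ward closures or a gradual change in case mix would make neighbouring weeks more alike than distant ones. Such correlation makes the difference between the two runs more variable. Compound symmetry cannot represent it: given the random effects, it treats the weeks of a trial as independent, so the model's standard error is too small.

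Calling the matrix a working one suggests that it may be wrong without harm. That is true only when a robust variance is used. A likelihood-ratio test takes its reference distribution from the model, so a wrong matrix gives a wrong p-value. At stake is the 5% level of the test on which effectiveness will be declared.

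**Working it through.** **Inputs.** From the documents: 100 trials; observation of 6 to 15 months, about 26 to 65 weeks; one switch at 15% to 85% of the period in 5% steps; likelihood-ratio test at 5%; compound symmetry. Assumed, because the documents give no value: a weekly within-trial autocorrelation (rho) of 0 to 0.5, or a slow drift.

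**The plan's own figure.** The protocol states that "an effect size of *d*=0.57 can be demonstrated" with 100 trials. A two-sided t-test with 50 per group and d = 0.57 has power 80.6%, and the detectable d at 80% power is 0.566. The figure reproduces. However, "Sample size calculation is based on the assumption of a simple parallel group design", so no serial correlation enters it and it says nothing about the level of the mixed-model test.

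**Closed-form approximation.** For long AR(1) series, the variance of a block mean exceeds its value under independence by the factor (1 + rho)/(1 - rho). The true rejection rate of a nominal 5% test is then about 2 × [1 - Φ(1.96 / √((1 + rho)/(1 - rho)))].
- rho 0.1: factor 1.222, 1.96/1.106 = 1.773, rejection 7.6%
- rho 0.2: factor 1.5, 1.96/1.225 = 1.600, rejection 11.0%
- rho 0.4: factor 2.333, 1.96/1.528 = 1.283, rejection 20.0%
- rho 0.5: factor 3, 1.96/1.732 = 1.132, rejection 25.8%

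**Simulation with no effect, 100 trials.** The table gives the percentage of runs rejected by the model-based test under constant correlation. Observation is 26 to 65 weeks unless stated.

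| Fitted model (runs) | rho 0 | 0.1 | 0.2 | 0.3 | 0.4 | 0.5 |
|---|---|---|---|---|---|---|
| Trial intercept (1,000) | 3.2 | 5.8 | 10.0 | 13.9 | – | 24.7 |
| Trial intercept, all trials 65 weeks (1,000) | 5.2 | 7.4 | 11.4 | 13.6 | – | 26.1 |
| Within-trial estimator (1,000) | 5.1 | 7.5 | 9.0 | – | 20.3 | – |
| Trial effect and linear time (800) | 6.0 | 7.6 | 8.1 | – | 17.9 | – |
| Crossed intercepts for trial, site, week, season (300) | 6.3 | – | 10.7 | 14.7 | – | 18.3 |
| The same plus a trial-level time slope (300) | 6.3 | – | 10.0 | 14.3 | – | 19.0 |

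At a true 5%, the Monte Carlo standard error is √(0.05 × 0.95/1,000) = 0.7 points with 1,000 runs and 1.3 points with 300. The last two rows come closest to the planned random effects. They soften the inflation at rho 0.5 but do not remove it.

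**Slow drift.** Here the truth is an AR process with weekly phi 0.9 carrying 10-20% of the residual variance, plus white noise. With a linear time term in the model, the compound-symmetry test rejected in 8-14% (300 runs), 12.8-16.5% (400 runs) and 10.5-14.4% (800 runs).

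**Low counts.** With Poisson weekly counts of mean 0.25 to 1 and a slowly varying rate, the lag-1 correlation of the counts is only about 0.06 to 0.27. Rejection was still 12.2-31.9%, against 4.7% (mean 0.5) without serial correlation.

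**Alternatives on the same kinds of data.**
- Trial-clustered errors: 5.3%, 4.9%, 5.2% and 5.2% at rho 0, 0.1, 0.2 and 0.4 (1,000 runs); 3.9-6.4% across AR(1) and drift settings (800 runs).
- Trial intercept plus AR(1), when the truth is AR(1): 4.3% at rho 0.3 and 7.3% at rho 0.5 (300 runs, compatible with 5%).
- Trial intercept plus AR(1), when the truth is slow drift plus noise: 11.0% and 11.5% (400 runs). At 11% the standard error is √(0.11 × 0.89/400) = 1.6 points, so this is not 5%.

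**Unstructured matrix.** It has T(T + 1)/2 parameters: 65 × 66/2 = 2,145 at 65 weeks, 26 × 27/2 = 351 at 26 weeks, and 15 × 16/2 = 120 on monthly data over 15 months. If observation lengths were uniform over 26 to 65 weeks (an assumption), about 35 of 100 trials would reach week 52 and 2 to 3 would reach week 65.

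**The case against.** The strongest reply is that the authors saw the threat. An autoregressive analysis is pre-specified, and so are monthly frames and mean-value statistics. If the last means a comparison of before and after means within each trial, which the wording leaves open, it does not depend on the weekly covariance at all. A paired t-test on trial means rejected in 4.3-6.0% of runs in every simulated setting, although it does not adjust for a common time trend. A reader might infer that the plan ignores serial correlation; the text does not support that. What stands is the hierarchy: these analyses may reveal a problem, but effectiveness is declared from the primary test.

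A second reply is that the random effects for site, season and time absorb the correlation. They cover variation shared across trials or a smooth trend. Correlation specific to a trial's own weeks remains, as the crossed-effects rows show.

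A third reply is that a robust variance could be specified in an analysis plan that is not shown. But the protocol does not leave the test open. It names the likelihood-ratio test, which does not use a robust variance.

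It is also fair that the unstructured matrix is only a sensitivity analysis and cannot change the primary conclusion. That part is minor.

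**Conclusion.** The point holds conditionally. If weekly recruitment within a trial has positive serial correlation, the primary test exceeds its 5% level: about 6-8% at rho 0.1, 8-11% at 0.2, 17-20% at 0.4, and about 8-16% under the slow drift described. At rho 0 the level is held, at about 5%, and negative correlation would make the test conservative.

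A reader might infer that the 5% level is certainly broken. The documents do not support that, because they contain no autocorrelation; every figure above 5% rests on an assumed one. Nor does it follow that promoting the autoregressive analysis would settle the matter, since AR(1) did not restore the level under slow drift plus noise.

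Effectiveness requires a positive effect, so about half of the rejections would be false claims of benefit: at rho 0.2, about 4-5.5% against a nominal 2.5%. This is a cheap and worthwhile improvement to the primary analysis, not a fatal flaw.

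**What to change.** Keep the linear mixed model and its estimate, and change the basis of inference. Take the primary p-value and confidence interval from either of these:

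1. sandwich errors clustered by trial, with a small-sample correction; or
2. a randomization test that re-draws the switch fractions from the block scheme described under Study design, including the rounding of switch dates to the first or 15th of a month.

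An AR(1) working matrix may be used within the first option, but should not be relied on alone. The existing sensitivity analyses can stay. Saying whether the mean-value statistics are within-trial before/after comparisons would make them more useful.

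As a minor change, replace the weekly unstructured matrix with Toeplitz, or use unstructured only on monthly data.

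The cost is wording and analysis code, with no new data. Intervals will be wider where autocorrelation exists, and power lower accordingly.
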